### 2.4. Sample size and sampling strategy

The planned study sample comprises 75 participants: 25 patients with a clinical diagnosis of moderate or severe unipolar depression and 50 healthy controls. Patients will be assessed at five time points: baseline (V0) and four monthly follow-up visits at 30, 60, 90 and 120 days, each with an allowed window of ±7 days. Assuming complete follow-up, this will generate 125 longitudinal voice recordings in the clinical group. Healthy controls will undergo a single baseline assessment, generating 50 voice recordings. The planned dataset therefore comprises 175 voice recordings.

The sample size was defined pragmatically as a feasible recruitment target for a hospital-based feasibility and methodological pilot study conducted in a real-world clinical setting. The study is not intended as a definitive diagnostic accuracy trial powered to estimate the performance of a final clinical classifier. Rather, it is designed to evaluate the feasibility, standardization, reproducibility and analytical validity of a multimodal voice- and speech-based methodology for depression assessment and longitudinal monitoring.

As a quantitative sensitivity analysis, a baseline comparison of 25 patients and 50 healthy controls, with a two-sided significance level of 0.05 and 80% power, would detect a standardized mean difference of approximately Cohen’s d = 0.70. The study is therefore primarily sensitive to moderate-to-large effects. This is presented as a sensitivity analysis because reliable prospective effect-size estimates are not available for the multiple exploratory speech-derived variables included.

The sampling strategy will be consecutive and non-probabilistic. Eligible patients will be recruited during routine clinical care in the Department of Psychiatry, including both outpatient consultations and inpatient care. Healthy controls will be invited by members of the research team and assessed after confirmation of eligibility.

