Although a balanced baseline comparison between patients and healthy controls would be methodologically desirable, the final allocation was defined according to feasibility considerations. Healthy controls will be individually matched to patients by age and sex whenever feasible. If individual matching cannot be achieved, control recruitment will be guided by the age and sex distribution of the patient group to obtain group-level frequency matching as closely as possible. Recruitment of clinically characterized patients with moderate or severe depressive disorder is expected to be more demanding because it requires repeated clinical assessments and longitudinal follow-up. In contrast, healthy controls require only a single baseline visit, allowing the inclusion of a larger control group without substantially increasing study burden. Therefore, the study will include 25 patients and 50 healthy controls. This design is expected to strengthen the baseline characterization of non-depressed speech patterns while preserving the longitudinal focus of the clinical cohort.

At participant level, baseline analyses will compare patients and healthy controls, whereas longitudinal analyses will focus on within-patient changes across repeated assessments. For predictive modeling, the imbalance between groups will be explicitly considered through appropriate analytical strategies, such as participant-level data splitting, balanced resampling, class weighting or sensitivity analyses when applicable.

Given the pilot nature of the study and the moderate sample size, classifier performance estimates will be interpreted as exploratory and hypothesis-generating. The study will prioritize transparent feature extraction, reproducible preprocessing, clinically interpretable modeling and longitudinal within-subject analysis over the development of a definitive deployable diagnostic model. Model complexity will be limited in relation to the available sample size, and classifier performance estimates will be accompanied by confidence intervals whenever feasible.

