### 2.7. Statistical and analytical plan

The analytical strategy of the VOICE-DEP study is designed to support the primary and secondary objectives of the protocol while ensuring methodological transparency, reproducibility, and robustness. In accordance with the study design, the analysis will address three complementary dimensions: (i) descriptive characterization of the study sample and extracted variables, (ii) exploratory cross-sectional association and discrimination analyses between patients with depressive disorder and healthy controls, and (iii) longitudinal intra-individual modeling of changes in voice- and speech-derived variables in relation to clinical evolution.

First, a descriptive analysis will be performed for all study variables recorded in the case report form. Quantitative variables, including acoustic, paralinguistic, and linguistic features, will be summarized using means and standard deviations or medians and interquartile ranges, as appropriate according to their distribution. Qualitative variables will be described using absolute frequencies and percentages. This descriptive phase will include both baseline variables collected at V0 and longitudinal variables collected across repeated visits in patients. Age, sex, educational level and available socioeconomic-related variables will be compared between groups and considered as covariates in adjusted or sensitivity analyses when relevant imbalance is observed and the sample size permits stable estimation.

Second, the association between continuous voice- and speech-derived digital biomarkers and clinical severity measures will be explored using Pearson or Spearman correlation coefficients, depending on distributional assumptions. These analyses will focus on the relationship between multimodal voice-derived variables and clinician-rated depressive symptom severity measured with the MADRS, global clinical status measured with the CGI, and self-reported depressive symptom burden measured with the Patient Health Questionnaire-9 (PHQ-9).

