For diagnostic discrimination between patients and healthy controls, classification models will be developed and evaluated. The area under the receiver operating characteristic curve (AUC) will be used as the principal performance metric, and additional measures such as odds ratios and their corresponding 95% confidence intervals will be reported where applicable. These analyses will be interpreted as exploratory because the study is a pilot methodological validation study rather than a definitive diagnostic accuracy trial.

Third, a systematic comparison between unimodal and multimodal approaches will be conducted. Unimodal models will include models based exclusively on audio-derived features or text-derived features, whereas multimodal models will combine acoustic, paralinguistic, and linguistic information. This comparison is intended to quantify the added value of multimodal integration beyond individual feature domains and is directly aligned with one of the predefined secondary objectives of the study.

Embedding-based acoustic features and contextual text embeddings will be evaluated exploratorily because previous studies suggest that they may capture clinically relevant patterns beyond predefined features [8,10,12,13]. Given their high dimensionality and limited interpretability, they will not constitute the primary analytical approach. Model specifications and extraction procedures will be fully documented to ensure transparency and reproducibility.

Longitudinal analyses will be used to evaluate the evolution of voice- and speech-derived digital biomarkers over time and their association with changes in depressive symptom severity and global clinical status. Because repeated assessments are obtained in the patient group at V0, V1, V2, V3, and V4, these analyses will account for within-subject correlation. Mixed-effects models and, where appropriate, finite-difference or change-score approaches will be used to examine intra-individual trajectories and their relationship with variation in MADRS, CGI, and PHQ-9 scores, as well as with relevant treatment-related variables. Treatment exposure and changes during follow-up will be included, where feasible, as time-varying covariates in the mixed-effects models. Treatment-specific analyses will be considered exploratory and will not be interpreted causally.

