Psychotic status will be considered as a potential confounder and included as a binary covariate when the sample permits stable estimation. Sensitivity analyses excluding patients with psychotic depression will be performed, while subgroup comparisons will be considered exploratory.

Regularized logistic regression will be the primary classification model, with a linear support vector machine and random forest models used for comparison. Missing data, including their frequency, pattern, and documented reasons, will be reported by variable and visit. Mixed-effects models will include a participant-specific random intercept, time as a fixed effect, and selected time-varying covariates; a random slope for time will be considered if supported by the data. The Benjamini–Hochberg procedure will control the false discovery rate within each feature family, and feature selection and hyperparameter tuning will be performed within each training partition.

Because repeated recordings from the same patient are not independent, all longitudinal analyses, predictive modeling and validation procedures will use participant-level data splitting and account for within subject correlation, in order to preserve the independence of training and test data. Specifically, all recordings from the same participant will be assigned exclusively to either the training or the test partition, in order to reduce optimistic bias due to repeated observations from the same individual and avoid information leakage. In this context, Leave-One-Group-Out cross-validation will be used as an appropriate validation framework for grouped repeated-measures data.

To improve clinical interpretability, feature attribution analyses will be performed using Shapley-based methods, including SHAP values where applicable. These analyses will help identify which acoustic, paralinguistic, and linguistic signals contribute most strongly to model predictions and will support the interpretation of the relative importance of different multimodal domains. No imputation for missing data will be applied. To maximize the data collection, quality control reviews will be conducted after every visit. A flexible time-window for visits and periodic reminder phone calls will be planned to reduce the risk of follow-up losses.

All analyses will be performed using Python v3.x or equivalent validated statistical software. Statistical significance will be considered at a two-sided threshold of p < 0.05.

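### Covariate adjustment, the plan's only stated handling of education and socioeconomic imbalance, does not remove confounding from the patient-control AUC

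*Protocol article*

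**What the plan says.** - **Design.** Section 2.4 plans 25 patients and 50 controls. "Healthy controls will be individually matched to patients by age and sex whenever feasible"; the fallback is "group-level frequency matching as closely as possible", again on age and sex. Education and socioeconomic status are not matching factors. Controls are invited by members of the research team.
- **Analysis.** Section 2.7 compares age, sex, education and available socioeconomic variables between the groups. They are then to be "considered as covariates in adjusted or sensitivity analyses when relevant imbalance is observed and the sample size permits stable estimation".
- **Metric and model.** For patients against controls, "The area under the receiver operating characteristic curve (AUC) will be used as the principal performance metric". "Regularized logistic regression will be the primary classification model". Where section 2.7 lists classifier inputs, it names speech features only.
- **Psychotic status.** Section 2.7 makes it a binary covariate if the sample allows, without naming the model it enters.
- **Features.** Table 3 includes lexical diversity, word count and sentence length, which may plausibly vary with schooling, and also many purely acoustic measures.
- **Status.** Sections 2.4 and 2.7 call the classifier results exploratory.

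**The concern.** Adjusting for a covariate removes confounding from a regression coefficient or an odds ratio, because the coefficient of interest is then read at a fixed covariate value. An AUC is different: it ranks every patient against every control on the fitted score, whatever their covariate values. Suppose patients have less schooling than controls.

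- Education left out of the score: features that track schooling still separate the groups.
- Education put into the score: it separates the groups directly.

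Neither route isolates depression, and section 2.7 names no step that would. The primary objective is discrimination by voice, so the headline figure could partly measure schooling. The same applies to age and sex if matching falls short.

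**Working it through.** **1. The plan's own figure.** Section 2.4 states that 25 against 50, "with a two-sided significance level of 0.05 and 80% power", "would detect a standardized mean difference of approximately Cohen’s d = 0.70". Check: d = (1.960 + 0.842) × √(1/25 + 1/50) = 2.802 × 0.2449 = 0.686; with the exact t distribution (73 df) it is 0.695. Power at d = 0.70 is 80.5% (t). The figure reproduces. For one normal feature, d = 0.70 corresponds to AUC = Φ(0.70/√2) = 0.690.

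**2. What an imbalanced covariate is worth on its own** (the sizes of imbalance are assumptions).
- Normal covariate: AUC = Φ(SMD/√2). SMD 0.2 gives 0.556; 0.358 gives 0.600; 0.5 gives 0.638; 0.7 gives 0.690.
- With no true difference, an SMD of at least 0.358 in either direction arises by chance in 2 × [1 − Φ(0.358/0.2449)] = 14% of samples of this size.
- Psychotic status is absent in controls by eligibility. Entered in the patient-control classifier, it alone gives AUC = 0.5 + q/2, where q is the share of patients with it: 0.60 if q = 20% (assumed).

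**3. What reaches the AUC if the covariate is left out.** For one feature with no depression effect and correlation ρ with the covariate, AUC = Φ(ρ × SMD/√2). Examples: ρ = 0.3, SMD 0.36 gives 0.530; ρ = 0.5, SMD 0.5 gives 0.570; ρ = 0.7, SMD 0.7 gives 0.636.

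**4. Trained classifier, no depression effect.** Ridge logistic regression trained on 25 against 50 and tested on 500 against 1,000 new people; 2 or 6 features, half of them correlated 0.3 or 0.6 with the covariate; 300 runs per setting.

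| SMD | features only | covariate added | features residualised |
|---|---|---|---|
| 0.36 | 0.51-0.53 | 0.55-0.57 | 0.50-0.51 |
| 0.5 | 0.52-0.56 | 0.58-0.61 | 0.51 |
| 0.7 | 0.53-0.61 | 0.64-0.67 | 0.51-0.52 |

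**5. Three education levels, no depression effect.** Ten features, 5-fold cross-validation, 25 against 50. Assumed low/middle/high shares, scored 0, 1, 2:
- Large gap: patients 50/30/20%, controls 20/30/50%. Means 0.70 and 1.30, variance 0.61 in each group, so SMD = 0.60/0.781 = 0.77.
- Moderate gap: patients 35/35/30%, same controls. Means 0.95 and 1.30, variances 0.6475 and 0.61, so SMD = 0.35/0.793 = 0.44.

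| Setting | features only | education added | same-education pairs |
|---|---|---|---|
| Large gap, all 10 features correlated 0.4 | 0.61-0.62 | 0.63-0.65 | 0.49-0.50 |
| Large gap, 4 of 10 correlated 0.4 | 0.57 | – | – |
| Large gap, all 10 correlated 0.2 | 0.54 | – | – |
| Moderate gap, all 10 correlated 0.4 | 0.53-0.54 | 0.55-0.56 | 0.48-0.50 |
| No gap | 0.50 | 0.50 | 0.48 |

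The ranges come from repeated runs. Values just under 0.50 also occur with no gap, so they are not an education effect. With an illustrative true effect and the large gap, the crude AUC was 0.74-0.77, against 0.65-0.68 when education was balanced; same-education pairs gave 0.65-0.70.

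**6. Precision.** The null standard error of the AUC is √[(25 + 50 + 1)/(12 × 25 × 50)] = 0.071. Same-education pairs under the large gap: share 0.5×0.2 + 0.3×0.3 + 0.2×0.5 = 0.29 of 25 × 50 = 1,250 pairs, about 360. Stratifying also by sex and three balanced age bands divides this by 6, leaving about 60.

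**The case against.** A reader might infer that the plan's remedy makes matters worse by feeding education to the classifier. The documents do not support that: the covariate sentence stands in the descriptive paragraph of section 2.7, the inputs named for the classifiers are speech features only, and odds ratios, for which adjustment works, are also to be reported. The plan may already keep covariates out of the score.

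A reader might also infer that an AUC above 0.6 is to be expected without any depression effect. That needs a large gap and either many features tracking education or education entered as a predictor. A moderate gap gives 0.53-0.56, within one null standard error of 0.50. The 10-feature runs also used 5-fold validation, whereas the plan uses Leave-One-Group-Out.

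Age and sex are addressed by matching, the classifier results are labelled exploratory, and an analysis plan that is not shown may hold further detail.

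All of this limits the size of the point. What stands is that section 2.7 does fix a strategy for imbalance, and that strategy does not act on the metric ranked first, on either reading. The exploratory label limits what may be claimed; it does not remove bias.

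**Conclusion.** The point holds in a limited form. If education or socioeconomic status differs between the groups, following section 2.7 leaves the patient-control AUC confounded, whether or not those variables enter the classifier. Under the 10-feature assumptions with no depression effect, the AUC is about 0.53-0.56 for a moderate education gap (SMD about 0.44) and about 0.54-0.65 for a large one (SMD about 0.77). The lower values apply when education is left out and few features track it, or all track it weakly. The gap and the correlations are assumptions; the documents supply neither. Without imbalance there is no bias from this source. Severity is moderate: a cheap improvement to an exploratory analysis.

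**What to change.** In section 2.7:
1. State that age, sex, education, socioeconomic variables and psychotic status are not predictors in the patient-control classifier.
2. Report, as a benchmark, the AUC of a model with age, sex and education alone, from the same cross-validation partitions.
3. Where relevant imbalance is observed, report a covariate-adjusted AUC beside the crude one. Either compare held-out scores only between patients and controls of the same education level, or residualise features on the covariates within each training partition (the check above fitted this in the training controls). Interpret discrimination in the light of both AUCs.
4. Keep covariate adjustment for the feature-level regressions and odds ratios.

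The cost is a little code and wording; Table 2 shows that age, sex and education are already collected at V0. The adjusted AUC will have a wider interval. Joint stratification by education, sex and age band would be too sparse with 25 patients (about 60 pairs in the example) and should not be the basis of the claim.

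### AUC cannot be computed within Leave-One-Group-Out folds, and pooling the out-of-fold scores biases it downward unless class weights are applied in each training partition

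*Protocol article*

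**What the plan says.** Section 2.7 of the protocol article fixes three things for the patient–control classification:

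- Metric: "The area under the receiver operating characteristic curve (AUC) will be used as the principal performance metric".
- Model: "Regularized logistic regression will be the primary classification model, with a linear support vector machine and random forest models used for comparison".
- Validation: "all recordings from the same participant will be assigned exclusively to either the training or the test partition", and in that setting "Leave-One-Group-Out cross-validation will be used as an appropriate validation framework for grouped repeated-measures data".

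The unit kept together is the participant, so on the natural reading the participant is the group left out. The same section places feature selection and tuning inside each training partition.

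Section 2.4 gives the numbers: "The planned study sample comprises 75 participants: 25 patients with a clinical diagnosis of moderate or severe unipolar depression and 50 healthy controls". On recordings it says "Assuming complete follow-up, this will generate 125 longitudinal voice recordings in the clinical group" and "Healthy controls will undergo a single baseline assessment, generating 50 voice recordings". It also says that group imbalance will be considered in predictive modelling. Class weighting and balanced resampling appear there as examples, to be used where they apply.

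The article does not say whether AUC is taken per fold or from pooled scores.

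**The concern.** An AUC compares the scores of patients with those of controls, so it needs both classes in the set where it is computed. A fold that holds one participant has only one class. Scores must therefore be pooled across models, and each of those models was trained on a slightly different class mix. The difference is tied to the label of the person held out, so it does not average away.

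Discrimination between patients and controls is part of the primary objective in section 2.1, and the gain from multimodal over unimodal models is secondary objective iii. A downward bias could make a useful set of features look weaker than it is. If the size of the bias differs between models, their comparison is affected too.

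**Working it through.** **The plan's own figure.** The article states no AUC. Its one computed figure is a detectable difference of about d = 0.70 (25 v 50, two-sided 0.05, 80% power). It reproduces: (1.960 + 0.842) × √(1/25 + 1/50) = 0.686 by the normal formula, 0.695 by the t distribution. It does not bear on the fold scheme.

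**Step 1: fold composition.** There are 25 + 50 = 75 folds. Of these, 25 hold one patient (one to five recordings, all positive) and 50 hold one control (one recording, negative). None holds both classes, so 0 of 75 fold AUCs are defined. This is exact.

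**Step 2: direction of the pooled bias.** The training share of patients is:

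- patient held out: 24/74 = 0.324 (all recordings: 120/170 = 0.706);
- control held out: 25/74 = 0.338 (all recordings: 125/174 = 0.718).

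If the penalty is so strong that only the intercept remains, the baseline score is ln(24/50) = −0.734 for every held-out patient and ln(25/49) = −0.673 for every held-out control. Every patient ranks below every control, and the pooled AUC is 0 instead of 0.5. Weights that equalise the classes in each training set remove the shift, and the same limit gives 0.5.

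**Step 3: size, by simulation.** These assumptions are not from the documents: ridge logistic regression, 20 Gaussian features of which 5 are shifted, intraclass correlation 0.5, 25 patients and 50 controls. There were 200 replicates at fixed penalty and 60 with the penalty tuned in each training set by inner deviance (grid 1 to 1000). Entries are pooled Leave-One-Group-Out AUC / mean fold AUC from stratified participant-level 5-fold, without class weights.

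| Setting | No signal | Shift 0.3 SD | Shift 0.7 SD |
|---|---|---|---|
| Penalty 1, baseline | 0.475 / 0.491 | 0.550 / 0.566 | 0.772 / 0.776 |
| Penalty 10, baseline | 0.461 / 0.491 | 0.576 / 0.590 | 0.771 / 0.779 |
| Penalty 100, baseline | 0.379 / 0.505 | 0.491 / 0.590 | 0.745 / 0.797 |
| Penalty 100, five recordings per patient | 0.425 / 0.506 | 0.544 / 0.599 | 0.788 / 0.815 |
| Tuned, baseline | 0.214 / 0.501 | 0.457 / 0.612 | 0.770 / 0.795 |

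The gaps are 0.004 to 0.030 at penalties 1 and 10 with baseline recordings, 0.027 to 0.126 at penalty 100, and 0.287, 0.155 and 0.025 when tuned. Standard errors of the means are at most 0.008 at fixed penalty and at most 0.024 when tuned.

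A separate tuned, unweighted simulation with the same number of features gave 0.20 v 0.53 with no signal, 0.66 v 0.71 at d = 0.5 and 0.83 v 0.84 at d = 0.8. A further run of 20 replicates, tuned on log-loss, gave 0.669 v 0.715 at d = 0.5 and 0.788 v 0.817 at d = 0.7. Tuned on AUC instead, it gave 0.629 v 0.765 at d = 0.7, so the tuning criterion matters as well.

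**Step 4: with class weights.** At fixed penalty the no-signal pooled AUC was 0.483 to 0.496, and the gap to 5-fold never exceeded 0.014. In tuned, weighted runs, gaps of about 0.01 to 0.05 remained.

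**The case against.** The strongest reply is that the plan does not commit to the failing configuration. Section 2.4 undertakes to deal with imbalance and names class weighting, which removes most of the bias. The rule for aggregating out-of-fold scores is also a detail that an article may leave to the full analysis plan. Both points are fair, and they are why the bias has to be stated as conditional. They do not remove the issue. The metric and the fold scheme are fixed in the article and do not fit together within a fold, and weighting is one option among several.

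A second reply is that the classifier results are declared exploratory, that the study disclaims being a definitive accuracy trial, and that a downward bias cannot create a false claim of discrimination. This lowers the severity. It does not excuse a systematic error of known direction, because the exploratory label covers imprecision. The correlations, mixed models and descriptive analyses are untouched.

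Two stronger readings are tempting. One is that the headline AUC is bound to be wrong, or that a useful model will look worse than chance. The documents do not support this: the size depends on penalty, signal, tuning criterion and weighting, none of which the article settles. The other is that the scheme produces a spurious multimodal gain. A difference of about 0.07 between 10 and 60 features (null AUC 0.36 v 0.43) does appear in simulation, but only at a fixed penalty with no signal. Section 2.7 requires tuning within each training partition, and no such gain was shown under that procedure.

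**Conclusion.** The point holds in conditional form. With the participant as the group, it is certain that no within-fold AUC can be computed, and that the training share of patients shifts against the held-out label (24/74 v 25/74). For an unweighted penalised logistic model, the pooled AUC is therefore biased downward.

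The size rests on the simulation assumptions above. It is about 0–0.03 with a weak penalty or strong signal, about 0.05–0.15 with a strong or tuned penalty and weak to moderate signal, and about 0.3 with a tuned penalty and no signal. The AUC-tuned run (gap 0.136 at d = 0.7) shows that a strong signal does not always protect. Class weights remove most of the bias.

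Because the bias varies with penalty and signal strength, it may not cancel in the unimodal versus multimodal comparison; this is plausible but not demonstrated for the planned tuning. The matter should be fixed before analysis. It does not invalidate the study.

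**What to change.** Replace Leave-One-Group-Out with repeated, stratified, participant-level 5-fold cross-validation, so that each test fold holds 5 patients and 10 controls. Compute AUC within each fold and average over folds and repeats, with the number of repeats fixed in advance. Use stratified participant-level splits for inner tuning too. Each fold AUC then comes from one model, so an intercept shift cannot alter the ranks, and the training share of patients is 20/60 throughout.

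If Leave-One-Group-Out is kept, commit to class weights within every training partition, state that AUC is computed from pooled out-of-fold scores, and report that a small downward bias remains.

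The cost is a sentence or two. Each 5-fold model trains on 60 participants instead of 74, which makes the estimate slightly pessimistic. No data need to be recollected. Section 2.10 plans analysis for February 2028, so the change can be made before any result is seen.
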